### Monitoring and safety

#### Data review

Given the low physical risk of walking and meditation, a separate data monitoring committee will not be formed. The research team will review pooled data for any unexpected patterns.

#### Handling adverse events

Participants will be asked to report any discomfort during or after sessions. All reports will be logged. Any serious incident (like a fall) will lead to immediate medical care and reporting to the ethics committee within a day.

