### Intervention

The interventions will consist of eight sessions, each lasting 120 min, held 3 days a week in an outdoor natural setting. Including 1 h of travel time, each session will last approximately 3 h. To facilitate participation, round-trip transportation will be arranged by the researcher using a bus service from local health centers to the session venue. Participants will gather at their assigned health center and will be returned there after each session. Each intervention session will be supervised by the researcher, accompanied by two trained health liaisons. These liaisons, local community health volunteers, will assist in ensuring participant safety, responding to concerns, and supporting effective engagement during each session. Participants will be advised to bring appropriate outdoor clothing, comfortable footwear, water, and any necessary medications. The researcher will use a session checklist to ensure all protocol components (e.g., warm-up, 50-min core activity, and discussion) are delivered. Participant attendance and engagement will be recorded.

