### Control group

The control group will not receive any specific intervention during the study period. Instead, the participants will continue to receive standard care and support from their local healthcare centers. This approach will allow for a comparative analysis of the effects of the interventions by assessing differences in outcomes between the intervention and control groups. However, to ensure that control group participants also benefit from similar activities, they may be invited to participate in comparable sessions after the completion of the study. To adhere to ethical considerations and prevent feelings of disappointment or neglect in the control group, the following provisions will be considered:Provision of information and counselingMembers of the control group will receive comprehensive counseling regarding their health and well-being challenges. This counseling will include guidance on effective self-care and quality of life.Invitation to participate in future activitiesUpon completion of the main intervention, members of the control group may be invited to participate in similar activities. These activities will include educational sessions or social programs designed to promote participants’ health and awareness after the study concludes.Review and provision of resultsAt the end of the study, the overall research findings will be presented to all participants (both intervention and control groups). This action will foster a sense of involvement and value among participants and will provide them with information regarding the impact of the interventions.Creation of learning opportunitiesFollowing the intervention, educational sessions on topics related to mental and physical health in older adulthood will be organized for the control group. This will provide them with the opportunity to benefit from similar experiences, thereby upholding the ethical principles of the research in a way that ensures all participants, including members of the control group, will gain from their participation.

The following diagram will illustrate the anticipated impact of the interventions on mental health and cognitive empowerment in older adults. The walking group with meaningful conversation is expected to demonstrate greater improvements in mental vitality, whereas the meditation group is expected to show more progress in cognitive empowerment. The control group is expected to experience fewer changes (Fig. 2).

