### Follow-up

To minimize intervention attrition rates and ensure participant retention, several strategies will be implemented:*Regular follow-up*: Weekly reminder phone calls or messages will be sent to participants to notify them of upcoming sessions and to emphasize the importance of their attendance. Local healthcare staff, health ambassadors, and liaisons will also maintain regular contact with participants to reinforce their sense of commitment to the study.*Supportive and motivational environment*: Participants will be continuously reminded of the significance of their participation and the potential benefits of the study on their well-being. A social and interactive atmosphere will be fostered during the sessions to promote a sense of belonging and motivation to remain engaged throughout the study.*Family and caregiver involvement*: Family members will be encouraged to support their older adult relatives by facilitating their attendance at sessions. Caregivers will be educated on their important role in promoting consistent participation and adherence to the study protocol. These strategies will help reduce attrition, enhance participant satisfaction and engagement, and ensure the collection of valid and reliable data.Furthermore, to facilitate attendance, round-trip transportation to the session venue will be provided. All participants will receive a summary of the aggregate study findings upon completion as tokens of appreciation.

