### Data collection

Data collection will be conducted in a structured and systematic manner to ensure the reliability and validity of the results. This process will begin with the acquisition of the necessary ethical and administrative approvals prior to any data collection activities. The study will also be registered with the Iranian Registry of Clinical Trials (IRCT20241023063481N1). To ensure data quality, all research personnel received standardized protocol training. The researcher will visit the selected health centers, explain the objectives and methodology of the study to the managers and healthcare staff, and obtain their consent to cooperate. Following this, the process of informing potential participants will begin. Assessments occur at three time points: baseline (pre-intervention), immediately post-intervention (week 8), and at a 3-month follow-up. At each stage, outcome measures (cognitive empowerment, mental vitality) are collected. To uphold the intention-to-treat principle, all participants initially randomized will be included in the final analysis. Individuals who choose to discontinue the active intervention sessions will still be invited to provide outcome data at the designated follow-up assessments (week 8 and 3 months), subject to their ongoing consent for this limited study involvement. Copies of all paper-based data collection forms are retained as study records and are available for review upon reasonable request.

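### Adverse events are solicited only around sessions, which the control arm does not have, so harms in an active arm could not be fairly set against control

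*Protocol article*

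**What the plan says.** The section on handling adverse events gives one rule for eliciting harms: "Participants will be asked to report any discomfort during or after sessions". It adds "All reports will be logged" and "Any serious incident (like a fall) will lead to immediate medical care and reporting to the ethics committee within a day". Neither of these two sentences names an arm or is limited to sessions.

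Sessions belong to the two active arms. Under Intervention: "The interventions will consist of eight sessions, each lasting 120 min". Under Control group: "The control group will not receive any specific intervention during the study period". Afterwards, "they may be invited to participate in comparable sessions after the completion of the study".

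For the assessments common to all arms (baseline, week 8, 3 months), the Data collection section says: "At each stage, outcome measures (cognitive empowerment, mental vitality) are collected". The Posttest and Follow-up (long-term evaluation) sections name the same two scales. The retention measures include that "liaisons will also maintain regular contact with participants to reinforce their sense of commitment to the study"; asking about harms is not given as a purpose of that contact.

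Under Statistical methods, the three pre-planned comparisons concern cognitive empowerment. Under Data review, the team looks at pooled data.

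**The concern.** The rule ties the question about harms to an event that one arm of three never has. Falls, injuries and new illness occur in women aged 60 and over with or without a walking programme, and the protocol itself uses a fall as its example of a serious incident. The control arm is what would separate background events from events due to the programme, and it can do so only if its members are asked in the same way.

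There is also a gap in time. Solicitation stops with the last session, while follow-up runs for a further 3 months. If a report of this trial set active-arm harms beside control harms, part or all of any excess could come from who was asked. The abstract hopes that the findings will support community programmes, so readers are likely to look for such a table.

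**Working it through.** The plan states no adverse event rate, safety test or safety sample size, so there is no figure to reproduce. The check is first a reading of who is asked and when.

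| Period | Walking | Meditation | Control |
|---|---|---|---|
| During or after sessions | asked | asked | no sessions |
| Week-8 assessment | two outcome scales | two outcome scales | two outcome scales |
| After last session to 3 months | no question described | no question described | no question described |
| 3-month assessment | two outcome scales | two outcome scales | two outcome scales |
| Volunteered report or known serious incident | can be recorded | can be recorded | can be recorded |

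The arms differ only in the first row, and there the two active arms agree with each other.

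**Direction and form of the distortion.** Let r be the share of an active arm with an event recorded in the session period, and s the fraction of comparable control events that gets recorded. With equal true risk and full recording in the active arm, the apparent difference is r − r·s = r(1 − s). With s = 0 it equals r. With s = 1 it is zero.

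**Illustration. All event risks here are assumptions.** The arm size is 37 (Sample size section). Assume a background risk of 5% to 15% over about 21 weeks (8 weeks plus 3 months taken as 13 weeks), at a constant rate. Only the session period is solicited.

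- Sessions spread over 8 weeks (abstract): r = 0.05 × 8/21 = 1.9% to 0.15 × 8/21 = 5.7%. Expected events per active arm: 37 × 0.05 × 8/21 = 0.7 to 37 × 0.15 × 8/21 = 2.1.
- Eight sessions at 3 a week (Intervention section): 8/3 = 2.67 weeks. r = 0.05 × 2.67/21 = 0.6% to 0.15 × 2.67/21 = 1.9%. Expected events: 37 × 0.05 × 2.67/21 = 0.2 to 37 × 0.15 × 2.67/21 = 0.7.

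The project management plan (Table 2) gives 1 month for the sessions, which lies between these. The three durations disagree and need to be reconciled. The range above covers them.

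**Would a test be misled?** Exact binomial enumeration with a two-sided Fisher test at 0.05, 37 per arm and equal true risk:

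| True risk in period | Rejects, no control events recorded | Rejects, half recorded | Rejects, equal recording |
|---|---|---|---|
| 5% | 1% | 0.4% | 0.3% |
| 10% | 16% | 3.5% | 1.5% |
| 20% | 78% | 14% | 2.6% |
| 30% | 98% | 25% | 2.9% |

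At low risks the harm would lie in the tabulated counts and how they are read. A test would be clearly misled only if events were common, as minor complaints might be.

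**The case against.** The strongest reply is that this affects no planned analysis. The aims and outcomes contain no safety endpoint, the three comparisons are of cognitive empowerment, and safety data are reviewed pooled. That stands: the bias is conditional on someone comparing harms with control.

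Second, a reader might infer that the control arm records no harms by design. The text does not say so. Reports are logged and serious incidents are passed on without restriction by arm, and controls have some contact through counselling and liaisons. A control fall that became known would be recorded. What is absent is any described way of asking for it.

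Third, a reader might infer that every between-arm safety comparison is biased. Walking and meditation have the same number and length of sessions and the same question, so that contrast escapes this mechanism.

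Fourth, one might apply a 5% to 15% risk to the whole 5 months and claim a spurious excess of 5 to 15 percentage points. That would need full recording in the active arms for 3 months after the sessions, which the described collection does not provide.

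Finally, this is a condensed article. The schedule figure and data collection forms are not shown, and the Data collection sentence does not say that nothing else is asked. That limits certainty. Still, the article has a section devoted to this subject, and the rule it fixes there is asymmetric.

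**Conclusion.** The point holds in a limited form. As described, harms are actively sought in two arms, around sessions only, and in the third arm not at all. Harms in either active arm cannot then be validly set against control, and events after the last session are left to spontaneous report in every arm. The primary analysis is untouched.

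The size cannot be derived from the documents. Under equal true risk and no recording in controls, the spurious difference is the recorded active-arm share in the session period. That is about 0.6 to 5.7 percentage points under the assumed 5% to 15% background risk, and less if some control events come to light. Equal questioning would not let 37 per arm establish equal safety. It would give an unbiased description. This is a modest but worthwhile correction.

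**What to change.** At week 8 and at 3 months, put the same short fixed questions to all three arms: falls, injuries, new health problems and hospitalisation since the last assessment. Tabulate the answers by randomised arm. Keep the session log as separate tolerability data for the active arms. If this is not done, state that harms will be described for the active arms only, without comparison with control. If the forms that are not shown already contain such questions, saying so in the adverse events section settles the matter.

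Both assessments already take place, so no extra staff or visits are needed. The price is a little added burden for participants and some recall error, particularly over the 3 months to the last assessment. According to the Trial status section, recruitment had not started at version 1.0; if it has since begun, the change should be dated and applied to all arms from the same point.

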### Posttest (immediate follow-up)

Upon completion of the 8-week intervention period, a posttest will be administered to evaluate the immediate effects of the intervention on the participants. This assessment will include questionnaires on cognitive empowerment and mental vitality to identify any changes in the measured outcomes. The comparison will help determine the immediate impact of the intervention.

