### Follow-up (long-term evaluation)

Three months after the intervention, a follow-up evaluation will be conducted to assess the sustainability of the intervention’s effects. Follow-up data will be used to examine any lasting changes in cognitive empowerment and mental vitality. This period will be essential for determining whether the intervention has long-term benefits or if observed improvements were temporary. Throughout the data collection process, the researcher will ensure that all procedures are implemented in a standardized manner to maintain consistency across participants and measurement time points.

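### Adverse events are asked about only around sessions, which controls do not have, so a by-arm harms count would rest on unequal questioning

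*Protocol article*

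**What the plan says.** Under Handling adverse events, the collection rule is: "Participants will be asked to report any discomfort during or after sessions". Reports are logged. A serious incident, with a fall as the example, leads to immediate care and a report to the ethics committee within a day.

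Who has sessions is settled elsewhere. Under Intervention: "The interventions will consist of eight sessions". Under Control group: "The control group will not receive any specific intervention during the study period". Controls may be offered comparable activities only once the study is over.

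Three sections describe the assessments that all arms share:
- Data collection: "At each stage, outcome measures (cognitive empowerment, mental vitality) are collected".
- Posttest (immediate follow-up): "This assessment will include questionnaires on cognitive empowerment and mental vitality to identify any changes in the measured outcomes".
- Follow-up (long-term evaluation): "Follow-up data will be used to examine any lasting changes in cognitive empowerment and mental vitality".

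None of them mentions an adverse event question. Two other contacts could reach controls. The section on retention (Follow-up) says "Weekly reminder phone calls or messages will be sent to participants to notify them of upcoming sessions" and adds regular contact by local health staff and liaisons to sustain commitment. The Control group section offers counselling on health and self-care, without saying when.

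**The concern.** The stated rule makes the chance of being asked depend on the allocated arm. A woman in an active arm who falls at home can be prompted to mention it at her next session. A control with the same fall has no matching prompt in the article. A table of logged events by arm would then mix any effect of the activity with the effect of being asked.

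This matters because the interventions take women aged 60 or over on outdoor sessions, one arm with a 50-minute walk, and because the article relies on low physical risk to do without a monitoring committee. The randomised control arm is the natural check on that premise. Unequal questioning could suggest harm where there is none, or hide a reduction in falls. Events that were never asked about cannot be recovered at the analysis stage.

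**Working it through.** **Step 1: occasions for being asked, from the text.**

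| Contact | Each active arm | Control | Adverse event question described? |
|---|---|---|---|
| Sessions (Intervention; Control group) | 8 per woman | 0 | Yes |
| Weekly reminders, local staff contact (Follow-up) | Yes | Staff contact, if not limited to active arms | No; stated purpose is attendance and commitment |
| Counselling (Control group) | Not stated | Yes, timing not given | No |
| Week 8 and 3-month assessments | Yes | Yes | No |

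With 37 women per arm (Sample size) and full attendance, the rule gives 37 × 8 = 296 woman-sessions with a prompt in each active arm and 0 in the control arm. The imbalance belongs to the session period. During the 3-month follow-up no arm has session prompts.

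**Step 2: size of the distortion.** The article gives no event rates or reporting rates, so every value below is an assumption. Let r be the true risk, equal in both arms, and let a and c be the proportions of events recorded in an active arm and in controls.

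- Recorded risks: r × a and r × c
- Recorded risk ratio: (r × a)/(r × c) = a/c, whatever r is
- Spurious risk difference: r × (a − c)

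| Assumed a, c | Ratio a/c | Spurious difference at r = 5%, 10%, 20% |
|---|---|---|
| 90%, 50% | 1.8 | 2.0, 4.0, 8.0 points |
| 90%, 25% | 3.6 | 3.25, 6.5, 13.0 points |
| 50%, 25% | 2.0 | 1.25, 2.5, 5.0 points |
| 90%, 90% | 1.0 | 0, 0, 0 points |

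At r = 20%, the expected recorded cases per 37 women are 37 × 0.20 × 0.90 = 6.7 in an active arm. In controls they are 37 × 0.20 × 0.50 = 3.7 or 37 × 0.20 × 0.25 = 1.9. The direction depends on a exceeding c, which is what asking only one side would be expected to produce.

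**Step 3: a true benefit.** Suppose walking halves falls, 10% against 20%, a true ratio of 0.5. With a = 90%, the recorded ratio is (0.10 × 0.90)/(0.20 × 0.50) = 0.9 at 50% control recording, and (0.10 × 0.90)/(0.20 × 0.25) = 1.8 at 25%. The benefit would almost vanish or appear as harm.

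**Step 4: what equal questioning leaves.** With a = c the ratio returns to the true value, but precision stays poor. At 10% in each arm, the 95% half-width for a difference is 1.96 × √(2 × 0.1 × 0.9/37) = 13.7 points. With 20% attrition (37 × 0.8 ≈ 30 per arm) it is 1.96 × √(2 × 0.1 × 0.9/30) = 15.2 points.

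**The case against.** **No harms comparison is promised.** The aims, hypothesis, outcomes and statistical methods contain none, and the adverse event section concerns care, logging and reporting. This stands, and it limits the weight of the point. It does not remove it: the collection rule is stated, differs by arm, and would shape any safety statement made against control.

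**The gap is partly read from silence in a condensed article.** The assessment sections do not say that nothing else is asked, and the data collection forms and data management plan are available on request. A visit form could already carry an adverse event item. This stands as a caveat: what can be said is that the article describes no such question.

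**Controls are not out of reach.** Local staff contact, counselling, usual care and two assessments all give a control the chance to mention a fall, and the serious incident rule is not confined to sessions. A reader might infer that no control event can ever be logged. The text does not support that; such reports are possible but unsolicited.

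**Pooled review.** The Data review section says "The research team will review pooled data for any unexpected patterns". A reader might infer that this rules out a comparison of arms. It does not: it governs review by the team during the trial and does not bar a final table by arm. The Steering Committee also watches for serious safety concerns. The point rests on the collection rule alone.

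**The fix buys little precision.** True, as step 4 shows. It removes a bias without making the trial able to detect modest differences in harm.

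**Conclusion.** The point holds and is minor. As described, adverse events are solicited around sessions that only the active arms have, and no equivalent question to controls is described at the shared assessments. A by-arm comparison from that log would be biased against walking and meditation as long as events are recorded more completely in those arms. The amount is unknown. Under assumed recording of 90% in an active arm and 50% to 25% in controls, equal risks would appear as a ratio of 1.8 to 3.6.

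It would go too far to say that the trial's safety data can show nothing. Serious incidents in sessions are attributable to an arm and promptly reported, and control events can still come in. The primary and secondary efficacy analyses are untouched.

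**What to change.** Amend Handling adverse events so that women in all three arms are asked the same adverse event and fall questions, in the same words, at the existing week 8 and 3-month assessments. Include women who stopped sessions, whom Data collection already invites back. State that any description of harms between arms uses those answers only. Keep the session log for immediate care and ethics reporting, and report it separately as session-related events. If the visit forms already contain such questions, it is enough to say so. Data review needs no change.

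The cost is a few questions at two existing assessments and a short wording change. The drawbacks are recall over 8 weeks and then 3 months, self-report by women who know their arm, and the wide intervals shown above. The change gives equal questioning across arms at the end of the trial; it does not improve detection during the sessions.
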